### Strategies to improve adherence to interventions {11c}

Fidelity of the intervention will be assessed using the framework for behavioral interventions recommended by NIH [25, 26] as outlined in Table 2.

**Table 2 Tab2:** Framework for behavioral interventions recommended by National Institute of Health

Goal	Strategies
Provider requirements	Intervention nurses must be SCNs. SCNs work in dedicated cancer services and are primarily responsible for care of people at a specific phase or across all phases of the cancer journey or work in a broader context but provide a specialist resource in cancer control to a range of generalist providers (for example, a cancer nurse coordinator). SCNs meet the minimum standard required for specialist practice in cancer nursing as set out in the competency standards from Cancer Australia [27]. Therefore, the nurse delivering the GOSPEL I intervention requires the critical thinking, coordination, and collaboration competencies defined in the SCN competency standards.
Training providers	Training will be provided to the SCNs to ensure standardization of intervention delivery. Provision of a study manual to all SCNs which includes: • Generic study related information: standard operating procedures, study overview, reporting/documentation guidelines, communication flowchart, rationale for the study treatment, completion of survivorship care plan, self-management goal setting, and health coaching (including motivational interviewing) resources • Interventionist specific information: job description, intervention protocol, quality assurance, and monitoring processes Completion of the eviQ Cancer Survivorship Introductory Course (~ 4.5 h over 6 modules). This course was developed by the Australian Cancer Survivorship Centre in collaboration with Cancer Australia, Queensland University of Technology, and the University of Sydney and is available online free of charge. Completion of face-to-face training from the research team which includes self-management support in cancer care, motivational interviewing techniques, and setting SMART goals. Intervention-specific procedures required for this trial. Education and resources regarding MBS item numbers that facilitate the proposed Model of Care. Resources to support GPs in performing physical examination and blood analysis.
Delivery of intervention	Intervention procedures are monitored through completion of intervention component checklists to ensure that the intervention is delivered as intended. Intervention checklists are completing during the SCN-led clinic and GP case conferences to track protocol deviations. All nurse-led clinics will be recorded and checked by another member of the research team against the clinic checklist to allow protocol deviation tracking across interventionists and conditions. Minimizing contamination between conditions by training SCNs to address participant questions about randomization and their assigned condition using non-biased explanations. SCNs will be supported during a weekly 15–30-min meeting for the first 3 months of the trial between the SCN and CIA or project manager. In addition to ongoing troubleshooting and support, intervention fidelity will be closely monitored and will be discussed during this meeting.
Receipt of intervention	The SCP serves as a resource for a participant to understand and refer to whenever they are unsure of follow-up schedule and collaborative goal setting.
Enactment of treatment skills	Enactment of treatment skills includes processes to monitor and improve participant ability to perform treatment-related behavioral skills and cognitive strategies in relevant real-life settings as intended. This goal will be achieved by: - Ensuring participants are aware of the follow-up schedules and responsibilities of all health professionals - Ensuring participants will have a copy of the completed self-management care plan including all care responsibilities and goals set for the individual

### Relevant concomitant care permitted or prohibited during the trial {11d}

No concomitant care or intervention is prohibited during the trial.

### Provisions for post-trial care {30}

There is no specified ancillary or post-trial care for participants in this trial. However, it is expected that the SCP generated will have the value of informing longer-term updates of the SCP and future survivorship care.

### Outcomes {12}

The feasibility outcomes are recruitment and acceptability of the intervention based on completion rates and semi-structured interviews. Participants or healthcare providers who opt into the 12-month semi-structured interview will be interviewed either face-to-face, by telephone, or through videoconferencing as per interviewee preference.

A range of patient-reported and process outcome measures will also be collected. Health-related quality of life as measured by the Functional Assessment of Cancer Therapy—Lymphoma (FACT-Lym) will be collected at baseline and 6 and 12 months post enrolment [28]. This valid and reliable tool captures key domains of health-related quality of life relevant to lymphoma and key symptoms that are relevant to the study population and sensitive to the GOSPEL I intervention. Additional outcomes include a range of patient-reported and process outcomes related to implementation as shown in Table 3.

**Table 3 Tab3:** Schedule for data collection during the GOSPEL 1 trial

	Study period					
	Enrolment	Allocation	Post-allocation			Close-out
Timepoint	Pre-baseline	Baseline	Baseline	6 months*	12 months*	18 months
**Enrolment**						
Eligibility screen	X					
Informed consent	X					
Allocation		X				
**Interventions**						
GOSPEL 1						
Usual care						
**Outcomes**						
Recruitment (feasibility)					**X**	
Barriers and facilitators of care: optional interviews (feasibility)					**X**	
Satisfaction of care					**X**	
Medications history			**X**			
HRQoL (FACT-Lym)			**X**	**X**	**X**	
Patient experience of care			**X**	**X**	**X**	
Symptom distress			**X**	**X**	**X**	
Comorbidity burden			**X**		**X**	
Dietary intake			**X**	**X**	**X**	
Physical activity			**X**	**X**	**X**	
Financial distress			**X**	**X**	**X**	
Employment interference			**X**	**X**	**X**	
**Participant characteristics**						
Demographics			**X**			
Clinical characteristics			**X**			
**Process Outcomes**						
Intervention fidelity: completion of checklists						**X**
Clinical encounters at cancer center						**X**
Cost analysis: resources to conduct the intervention						**X**
Safety indicators: clinical encounters, unscheduled clinic visits and rapid referrals back to acute care						**X**

*Post-baseline

### Participant timeline {13}

### Sample size {14}

In this pilot study, we will recruit 30 patients per arm in order to provide initial insights into the intervention feasibility and protocol as well as preliminary effect size estimates. The aim of this study is not hypothesis testing; the power level is therefore not a valid consideration for sample size [29, 30]. The sample size for this study (*n* = 60) falls within the range of sample size recommendations for pilot studies of this nature [29, 30].

### Recruitment {15}

Potentially eligible patients will be identified by clinicians and/or the research nurse through attendance at multidisciplinary team meetings and utilizing an existing clinical database. Potentially eligible patients will be identified; the treating clinician will ask the potential participant whether they agree to being contacted by the research nurse and will advise the research team accordingly. A patient brochure has been produced for clinicians to use when first discussing the study with potential participants. Only patients who have agreed to be contacted will be approached by the research nurse. Participants are given as much time as possible to consider their participation and are encouraged to take the information away and discuss joining the trial with family, friends, and their GP if they so wish to. Participants are also encouraged to ask the research nurses, their treating doctors, or nursing staff any questions in relation to their participation.

### Assignment of interventions: allocation

#### Sequence generation {16a}

Permuted block randomization will be conducted to assign participants to the control or intervention arms (Fig. 1). To ensure equal distribution of patients with different follow-up schedules, patients will be stratified by diagnosis (NHL vs HL) and follow-up pathway (group one: post-treatment vs group two: surveillance clinic).

**Fig. 1 Fig1:**
[figure not shown]
Comparison of usual care with standardized frequency and timing of follow-up for GOSPEL I components. Med history will be informed by pharmacy review prior to the SCN Clinic. Three-monthly follow-up schedule: flexibility 3 weeks ± the scheduled GP and specialist appointment permitted. Six-monthly follow-up schedule: flexibility 8 weeks ± the scheduled GP and specialist appointment permitted. > 2 years follow-up for usual care: indolent lymphoma, ongoing 6-monthly specialist review; aggressive lymphoma, 6-monthly specialist review (years 2–3), annual specialist review (years 3–5), discharge to GP after 5 years. SNC, Specialist Cancer Nurse; Tx, treatment; SCP, Survivorship Care Plan; Med, mediation; GP, general practitioner; H&P, history and physical examination. “History” includes review of patient experience of fevers, sweats, loss of weight, infections; “Physical Examination” includes check for lymphadenopathy, splenomegaly ± hepatomegaly; “Bloods” includes order and review of full blood count, urea and electrolytes, liver function tests, and lactate dehydrogenase. If the patient’s hematologist notes that additional clinic visits are clinically indicated, then they can schedule additional appointments

#### Concealment mechanism {16b}

Allocation sequence is implemented using sequentially numbered opaque, sealed envelopes. Envelopes are only accessed by the research nurse to randomize the patient once recruitment and baseline data has been collected.

#### Implementation {16c}

Allocation sequence is generated by a researcher not involved in recruitment or data collection. Patients are enrolled by a research nurse who collects baseline data prior to randomization. Enrolling nurses assign participants to the intervention after baseline data collection.

### Assignment of interventions: blinding

#### Who will be blinded {17a}

After assignment to the intervention, only outcome assessors and data analysts are blinded to group allocation. Where participants opt to complete their data collection by phone, they are advised not to reveal their group allocation to the outcome assessor. Due to the nature of the intervention, no participants or treating clinicians are blinded.

#### Procedure for unblinding if needed {17b}

No unblinding procedures required as only outcome assessors and data analysts are blinded.

### Data collection and management

#### Plans for assessment and collection of outcomes {18a}

Patient-reported outcomes are self-administered using online surveys or administered in person or via telephone with an outcome assessor trained in the administration of the study instruments.

A range of feasibility, patient-reported, and process outcomes related to implementation will be collected as shown in Tables 3 and 4.

**Table 4 Tab4:** Study outcome definitions

Outcome domain	Specific measurement	Metric and method of aggregation	Time point of interest
Health-related quality of life	The Functional Assessment of Cancer Therapy—Lymphoma (FACT-Lym) [28]	Effect of time on mean change score between groups	Baseline, 6 months, 12 months
Patient experience of care	Patient Assessment of Care for Chronic Conditions (PACIC)	Effect of time on mean change score between groups	Baseline, 6 months, 12 months
Symptom distress	Memorial Symptom Assessment Scale (MSAS) [31]	Effect of time on mean change score between groups	Baseline, 6 months, 12 months
Comorbidity burden	The Charleston Comorbidity Index (CCI) supplemented with items from Self-Administered Comorbidity Questionnaire (SCQ) [32]	Difference between mean change scores from baseline	12 months
Total leisure-time physical activity	Active Australia Survey [33]	Effect of time on mean change score between groups	Baseline, 6 months, 12 months
Usual vegetable intake and usual fruit intake	Two short dietary questions from the National Nutrition Survey [34]	Effect of time on mean change score between groups	Baseline, 6 months, 12 months
Financial distress	0–10 numerical analogue scale (where 10 is “a great deal” and 0 is “none”) [35]	Effect of time on mean change score between groups	Baseline, 6 months, 12 months
Employment interference	0–10 numerical analogue scale (where 10 is “a great deal” and 0 is “none”) [36]	Effect of time on mean change score between groups	Baseline, 6 months, 12 months
Satisfaction of care	0–10 numerical analogue scale (where 10 is “most satisfied” and 0 is “least satisfied”)	Difference in mean score between groups	12 months

Barriers and facilitators of care as measured by voluntary participation in semi structured interviews 12 months post enrolment. All intervention arm patients, lymphoma cancer nurses, GPs, and other nurses, and hospital- and community-based rehabilitation providers will be invited to participate in a one off semi-structured interview to discuss factors that facilitated or hindered the implementation of the GOSPEL I intervention.

Process outcomes, including completion of intervention components, as measured by completion of intervention materials such as clinic checklists, audio recordings of SCN-led clinics, and research nurse (RN) records in database will be checked for completion (Y/N) and duration (min) of SCN-led clinics.

Cost analysis will be conducted using hospital casemix data describing occasions of service including duration and indication and RN records in database. All resources required to conduct the intervention (e.g., staff, training, materials, communications, office space, utilities) will be monitored.

Safety indicators will be measured via hospital records to query the number of hospital clinical encounters, unscheduled lymphoma clinic visits, and rapid referrals back to acute care.

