## Statistical methods

### Statistical methods for primary and secondary outcomes {20a}

Descriptive statistics will be used to report on feasibility and process-related elements (e.g., recruitment, intervention, retention rates) as well as clinical and resource outcomes. Preliminary effect size estimates for patient and resource use outcomes will be calculated following intention-to-treat principles using linear mixed models. Models will include group, time, and their interaction and be adjusted by diagnosis and age. Balance of demographic variables between usual care and intervention group will be investigated using chi-square and *t* test and will be included in the model if found to be both significantly associated with the outcome and confounding the intervention. Assumptions of all models (normality, linearity, homoscedasticity) will be examined using the residuals of the model and will be described using mean, median, skewness, kurtosis, and plots such as histograms and QQ-plots. If assumptions are violated, models will be either bootstrapped or log transformation as appropriate.

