### Methods in analysis to handle protocol non-adherence and any statistical methods to handle missing data {20c}

Any discrepancies and missing data will be alerted and resolved with the relevant research team member(s) as soon as practical. All electronic CRFs will be maintained on the system with details of any changes logged accordingly. Preliminary effect size estimates for patient and resource use outcomes will be calculated following intention-to-treat principles using linear mixed models. Patterns of missing data will be examined using chi-square and *t* tests. Missing data for the outcomes will be accounted for by using mixed models allowing the use each available case by computing maximum likelihood estimates.

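### Table 4 does not name the between-arm contrast for the repeated patient-reported outcomes, and the stated model uses the baseline score less efficiently than it could

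*Protocol article*

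**What the plan says.** Table 4, in the section on plans for assessment and collection of outcomes {18a}, defines the outcome metrics. For FACT-Lym, PACIC, MSAS, physical activity, vegetable and fruit intake, financial distress and employment interference, the metric is "Effect of time on mean change score between groups", with baseline, 6 months and 12 months as the time points of interest. Two other rows are worded as plain contrasts at 12 months: comorbidity burden ("Difference between mean change scores from baseline") and satisfaction ("Difference in mean score between groups").

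The statistical methods section {20a} gives the analysis: "Preliminary effect size estimates for patient and resource use outcomes will be calculated following intention-to-treat principles using linear mixed models". It then lists the terms: "Models will include group, time, and their interaction and be adjusted by diagnosis and age". Beyond these, only demographic variables can enter, after a check of balance. The baseline value of the outcome is not named as a covariate, and no constraint on the baseline means is mentioned. Section {20c} adds: "Missing data for the outcomes will be accounted for by using mixed models allowing the use each available case by computing maximum likelihood estimates".

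On timing, the Outcomes section says that FACT-Lym "will be collected at baseline and 6 and 12 months post enrolment", and section {16c} says: "Patients are enrolled by a research nurse who collects baseline data prior to randomization". The sample size section sets 30 patients per arm and names preliminary effect size estimates as one purpose of the trial.

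**The concern.** There are two linked points.

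The first is the label. An effect of time is a movement over visits, whereas the information about the intervention lies in a difference between arms at a stated visit. The words about groups at the end of the entry suggest that a between-arm comparison of change is meant. Even so, the row does not say which visit carries it, and baseline cannot be a time point for a change score. With three visits the group-by-time interaction is two coefficients if time is categorical. If change at 6 and 12 months were the response, the interaction would be only the difference between the 6-month and 12-month effects. The contrast therefore has to be named.

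The second is precision. Baseline is measured before randomisation, so the true baseline means are equal in the two arms. A model that does not use this fact gives a contrast with more variance than necessary. The trial disclaims hypothesis testing, so for these outcomes the estimate and its interval are the product that a definitive trial would draw on.

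**Working it through.** **Inputs.** From the article: n = 30 per arm, 1:1 allocation, three visits, baseline before randomisation, and the model terms in {20a}. Assumed: outcome SD of 1 at each visit, complete data, and a baseline-to-12-month correlation r, which the article does not give; 0.3 to 0.9 is shown. The adjustment for diagnosis and age is left out of both sides of the comparison. The article states no standard error or interval width, so there is no figure of its own to reproduce.

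**Step 1: what the stated model estimates at 12 months.** Section {20a} does not say whether baseline is one of the responses or whether the response is the change score. Both readings lead to the same place.
- Baseline as a response: the arms have separate baseline means, and with complete data the 12-month interaction coefficient is the difference between arms in mean change.
- Change as the response: the 12-month arm contrast is again the difference in mean change.

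**Step 2: variances.**
- Difference in change: 2(1 − r) × 2/30
- Baseline-adjusted difference: (1 − r²) × 2/30
- Ratio of the two: 2/(1 + r)
- Baseline ignored, for reference: 2/30, giving SE √0.0667 = 0.2582

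At r = 0.5, for example, the change contrast has variance 1.0 × 0.0667 = 0.0667 (SE 0.2582) and the adjusted contrast 0.75 × 0.0667 = 0.0500 (SE 0.2236).

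| r (assumed) | SE, as planned | SE, adjusted | Variance ratio | Adjusted n per arm with the same precision, 30(1 + r)/2 |
|---|---|---|---|---|
| 0.3 | 0.3055 | 0.2463 | 1.54 | 19.5 |
| 0.5 | 0.2582 | 0.2236 | 1.33 | 22.5 |
| 0.7 | 0.2000 | 0.1844 | 1.18 | 25.5 |
| 0.9 | 0.1155 | 0.1125 | 1.05 | 28.5 |

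The planned SE is thus larger by 24%, 15%, 8.5% and 3%. Estimating the baseline slope in a sample of 60 multiplies the adjusted variance by about 1 + 1/56. The variance ratios become 1.51, 1.31, 1.16 and 1.03, so the gain remains.

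**Step 3: simulation.** 300 trials were simulated at each of r = 0.5 and r = 0.7, with three visits, a control-arm trend of 0.40 SD and a true 12-month effect of 0.30 SD.

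| Mean estimate (empirical SD) | r = 0.5 | r = 0.7 |
|---|---|---|
| Time coefficient at 12 months | 0.405 (0.180) | 0.398 (0.138) |
| Group-by-time at 12 months, stated model | 0.306 (0.257) | 0.295 (0.199) |
| Common baseline mean | 0.307 (0.226) | 0.295 (0.178) |
| Baseline as covariate, 12 months | 0.309 (0.229) | 0.293 (0.182) |

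The time coefficient recovers the control-arm trend. The interaction and both adjusted analyses recover the same treatment effect, and the adjusted ones are tighter by about the amount the formulas give.

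**The case against.** The strongest reply is that the Table 4 entry ends with a comparison between groups, that {20a} includes the group-by-time interaction, and that the comorbidity row shows between-arm change to be the quantity in mind. A reader might infer that a trend shared by both arms would be reported as the treatment effect. The documents taken together do not support that: the model contains the right term. What remains is loose wording that leaves the contrast and visit unnamed.

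A reader might also infer that the model targets the wrong estimand or throws the baseline data away. Neither holds. Under randomisation the stated model and the adjusted ones estimate the same effect without bias. A change contrast does use baseline: at r = 0.7 its SE is 0.200, against 0.258 with baseline ignored. It uses baseline inefficiently, and only below r = 0.5 does it do worse than ignoring it (0.306 against 0.258 at r = 0.3).

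Two further replies carry weight. First, {20a} does not say how baseline enters, and an unseen analysis plan could add it. The article does list the model terms, however, and the baseline outcome is not among them; the finding rests on that list. Estimation method and degrees of freedom are properly left to the analysis plan and form no part of this point. Second, feasibility is the objective, and a group-by-time mixed model is a valid and common choice. Wider intervals would not alter the feasibility conclusions. They would affect only the preliminary effect sizes, which the sample size section nevertheless names as a purpose.

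**Conclusion.** The point holds as a clarification plus an efficiency improvement. Table 4 should name the between-arm contrast and its visits, and the stated model gives a 12-month contrast that is unbiased but less precise than the data allow. The planned SE is about 15% larger than necessary at a correlation of 0.5 and 8.5% larger at 0.7, with 24% and 3% at the outer values of 0.3 and 0.9. These sizes rest on the assumed correlation, equal SDs at the visits and complete data, and they take no account of the diagnosis and age adjustment. The direction does not depend on which correlation in that range is right.

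**What to change.** In Table 4, replace the metric for the repeated patient-reported outcomes with the baseline-adjusted difference in mean score between arms at 6 months and at 12 months, each with a 95% confidence interval, and list only those two visits as the times at which the effect is estimated.

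In {20a}, keep the adjustment for diagnosis and age and state one of two models:
- the 6-month and 12-month scores as responses, with group, time, group-by-time and the baseline score as a covariate; or
- all three visits as responses, with one baseline mean common to both arms.

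The second keeps every patient with a baseline score in the likelihood, in line with the missing-data statement in {20c}. Either change is one of wording only: no new data, visits or patients are needed.
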